## 7. Sample size

The sample size was estimated based on the power to detect a clinically important 0.04 difference between groups in the primary outcome of the change in hemoglobin A1c. Based on previous trials, we expect a mean change in hemoglobin A1c in the control group of 0, with a standard deviation of 0.013 (1.3%). To detect a 0.004 (0.4%) absolute difference, a sample size of 332 (166 in each group) is required ( $\alpha$  0.05, power 80%). Assuming a 15% rate of drop-out or missing data (e.g. missing hemoglobin A1c measurement), 390 participants (195 in each group) are needed. A total of 390 participants were recruited, with 194 allocated to the intervention group and 196 allocated to the control group.

## 8. Statistical Analysis

### 8.1 Participant baseline characteristics

Participant characteristics at baseline will be summarized by trial arm. Continuous variables will be summarized using mean and standard deviation, or median and inter-quartile range if data do not have a symmetric distribution. Categorical variables will be summarized with counts and percentages. No statistical comparisons of participant characteristics at baseline will be performed between groups.

### 8.2 Analysis of primary outcome

Hemoglobin A1c will be compared between the intervention and control arm using analysis of covariance (ANCOVA). The covariates will be age, sex, household size, and condition (diabetes versus prediabetes). We will present results of the adjusted and unadjusted models. We will also describe for each group (intervention and control) the baseline, follow-up (6 month) and change (follow-up minus baseline) A1c using mean (with standard deviation) and median (with interquartile range).

In a sub-group analyses, we will assess whether there is a significant interaction between the mean change in hemoglobin A1c and (1) age, (2) sex, (3) condition ("prediabetes" and diabetes), (4) household size, (5) whether prescribed oral diabetes treatment (6) whether prescribed insulin.

We will also use chi-square tests to compare the proportion of participants with "pre-diabetes" (A1c 6.0 to 6.4) at baseline who convert to a normal hemoglobin A1c ( $<6.0$  %) and those who convert to diabetes (A1c  $\geq 6.5$ ), and the number of participants with diabetes at baseline (A1c  $\geq 6.5$ ) who convert to "pre-diabetes" (A1c 6.0 to 6.4) and to normal hemoglobin A1c ( $<6.0$ %).

For the primary analysis, a  $p$ -value of  $<0.05$  will be sufficient to reject the null hypothesis of no difference.

We will address missing outcome data using methods appropriate to their pattern which may include inverse probability weighted analysis. We will address missing baseline characteristic data using methods appropriate to their pattern which may include multiple imputation.

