### *Primary and secondary outcome measures*

The primary outcome will be the hemoglobin A1c at six months adjusted for the baseline measurement (the most recent result during the 3 months prior to enrollment). Hemoglobin A1c is associated with mortality and both macrovascular and microvascular complications of diabetes. Changes in hemoglobin A1c of 0.4 % or greater are associated with clinically important reductions in at least microvascular diabetes complications. The hemoglobin A1c will be obtained through chart reviews and by accessing laboratory data with consent. If more than one hemoglobin A1c measurement is available between 3 and 6 months (even though the test is usually done every 3 months or less frequently), only the later one will be used. The primary analysis will include all participants and report A1c as a continuous measure. We will also report the change in hemoglobin A1c by condition ("prediabetes" and diabetes), the number of participants with "pre-diabetes" (A1c 6.0 to 6.4) at baseline who convert to a normal hemoglobin A1c ( $<6.0\%$ ) and those who convert to diabetes ( $A1c \geq 6.5$ ), and the number of participants with diabetes at baseline ( $A1c \geq 6.5$ ) who convert to "pre-diabetes" (A1c 6.0 to 6.4) and to normal hemoglobin A1c ( $<6.0\%$ ).

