ask participants in the intervention group how often they accessed the food retailer, about their participation in educational and community building activities, about wasted food and about whether they would have wanted other foods to be provided.

We will perform a cost-effectiveness analysis from a societal perspective that considers direct and indirect costs of the intervention and direct and indirect effects including changes in healthcare utilization. We will assess the economic implications of the potential effects of the intervention including costs associated with primary care, emergency department use, and complications of diabetes based on previous studies of the association between hemoglobin A1c and health outcomes.

We will report demographic characteristics collected at the time of enrollment including age, sex, gender, education level, household income, income source, ethnicity, and medical comorbidities.

We will employ an intention to treat analysis. The primary analysis of the follow-up A1c (follow-up measurement) will be adjusted for baseline hemoglobin A1c and analysed using analysis of covariance (ANCOVA). Binary outcomes will be compared between groups using risk differences with 95% confidence intervals, and chi-squared tests to derive two-sided p-values. Continuous outcomes will be compared between groups using difference in means with 95% confidence intervals, and t-tests to derive two-sided p values. Count outcomes will be analysed using rate ratios from quasi-Poisson models with 95% confidence intervals and two-sided p-values, which will be adjusted for baseline values whenever available. Ordinal outcomes will be analyzed using ordinal regression.

Randomization will be stratified by site. We will report both the unadjusted analysis for the primary outcome and the analysis adjusted for age, sex, whether or not prescribed diabetes oral medicines at baseline, and whether or not prescribed insulin at baseline.

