### 5.3 Data preparation

The primary outcome of HbA1c at 6 months will be assessed via laboratory testing for study purposes or review of the electronic primary care record. This is a continuous variable. The primary outcome will be adjusted for HbA1c at baseline, which will be assessed via review of the electronic primary care record. This is a continuous variable.

Serum  $\beta$ -carotene and ascorbic acid levels at 6 months will be assessed via laboratory testing for study purposes.

Data on self-reported food security, self-reported financial security, and self-reported vegetable and fruit consumption will be collected through surveys administered online, over the phone, or in-person at 6 months. Baseline data on self-reported food security and baseline self-reported vegetable and fruit consumption were collected at through surveys conducted over the phone or in-person at the recruitment visit.

Self-reported health status will be measured on a 5-point likert scale, where participants were asked the standard question at follow-up "In general, how would you rate your health today?" Potential responses are: very good, good, moderate, bad, very bad and decline to respond.

Self-reported food security will be assessed using 6 standard and validated items adapted from the Canadian Community Health Survey (Household Food Security Survey Module), applied to the last 6 months (12). The instrument assesses worry about food running out due to financial constraints, food not lasting, and the inability to afford balanced meals using the following questions:

1. The food that you and other household members bought just didn't last, and there wasn't any money to get more. Was that often true, sometimes true, or never true in the past 6 months? Potential responses are: Often true, Sometimes true, Never true, Don't know/Refuse to answer
2. You and other household members couldn't afford to eat balanced meals. Was that often true, sometimes true, or never true in the past 6 months? Potential responses are: Often true, Sometimes true, Never true, Don't know/Refuse to answer
3. In the past 6 months, did you or other adults in your household ever cut the size of your meals or skip meals because there wasn't enough money for food? Potential responses are: Yes, No, Don't know/Refuse to answer

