### 6.2 Primary Outcome

The primary outcome is the change in hemoglobin A1c from baseline to follow up at six months. This is a continuous variable.

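### The primary ANCOVA in SAP 8.2 leaves out continuous baseline HbA1c, contradicting the protocol and SAP 5.3; coded as written it causes no bias but loses precision, and the estimate then depends on whether six-month HbA1c or change is modelled

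*Combined protocol and SAP*

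**What the plan says.** SAP 8.2 is the section that specifies the primary model. It says "Hemoglobin A1c will be compared between the intervention and control arm using analysis of covariance (ANCOVA", without stating whether the dependent variable is the six-month value or the change. It then lists the covariates: "The covariates will be age, sex, household size, and condition (diabetes versus prediabetes". It adds "We will present results of the adjusted and unadjusted models", but does not say which of the two is primary or what the unadjusted model contains.

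Other places read differently:

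- Protocol, Primary and secondary outcome measures: "The primary outcome will be the hemoglobin A1c at six months adjusted for the baseline measurement".
- Protocol, analysis paragraphs under Secondary outcome measures: the primary analysis of follow-up A1c "will be adjusted for baseline hemoglobin A1c and analysed using analysis of covariance (ANCOVA". The further adjusted analysis there uses age, sex, oral diabetes medicines and insulin.
- SAP 5.3: "The primary outcome will be adjusted for HbA1c at baseline, which will be assessed via review of the electronic primary care record". Baseline is described there as continuous.
- SAP 6.2: "The primary outcome is the change in hemoglobin A1c from baseline to follow up at six months". SAP 2.1 and SAP 7 also speak of change.

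**The concern.** The covariate list in 8.2 reads as complete, so a statistician who codes from that section fits a model without baseline HbA1c. Condition is not a substitute. It splits baseline HbA1c once, at 6.5, whereas the eligibility criteria admit values from 6.0 to 11, so all variation among participants with diabetes stays in the error term.

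Two things are at stake. The first is precision: baseline HbA1c is likely to be the strongest available predictor of six-month HbA1c. The second is uniqueness of the primary result. With baseline in the model it does not matter whether six-month HbA1c or change is the dependent variable. Without it, the two give different estimates and p-values against the single 0.05 threshold in 8.2, and the SAP does not settle which is meant.

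**Working it through.** **Inputs from the documents.** SAP 7 gives a difference of 0.4 percentage points, an SD of 1.3 points, alpha 0.05, power 80%, 332 evaluable participants (166 per group) and 15% loss. I take alpha as two-sided, which the protocol states for continuous outcomes in general. The protocol gives an SD range of 1.3 to 2; I use 1.3 because it is the SAP's value and reproduces 332.

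**Assumed inputs.** These are not in the documents: correlation r between baseline and six-month HbA1c of 0.5 to 0.8; equal SDs at the two times; condition explaining a share q of 20% to 50% of baseline variance; age, sex and household size explaining nothing further.

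**Step 1, the plan's own figure.** n per arm = 2 × (1.96 + 0.8416)² × 1.3² / 0.4² = 165.8, so 166 per arm and 332 in all. This matches. 332 / 0.85 = 390.6, against the stated 390. The calculation is a two-sample comparison of change and takes no credit for baseline adjustment.

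**Step 2, when the choice of outcome matters.** Write Y1 = a + bT + cY0 + other terms, where Y0 is baseline, Y1 is six-month HbA1c and T is treatment. Subtracting Y0 from both sides gives Y1 − Y0 = a + bT + (c − 1)Y0 + other terms. The treatment coefficient b, its standard error and its p-value are the same. If Y0 is not in the model the identity fails.

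**Step 3, power without condition.** Hold the SD of change at 1.3.

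- SD of six-month HbA1c: s = 1.3 / √(2(1 − r))
- Residual SD with baseline in the model: s√(1 − r²)
- Power = Φ(0.4 / (SD × √(2/166)) − 1.96)

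Example, r = 0.6: s = 1.3 / √0.8 = 1.453; residual SD = 1.453 × 0.8 = 1.163; 0.4 / (1.163 × 0.1098) = 3.13; power = Φ(1.17) = 88%.

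| r | s | Residual SD with baseline | Power: six-month only | Power: change only | Power: with baseline |
|---|---|---|---|---|---|
| 0.5 | 1.300 | 1.126 | 80.0% | 80.0% | 89.9% |
| 0.6 | 1.453 | 1.163 | 70.8% | 80.0% | 88.0% |
| 0.7 | 1.678 | 1.199 | 58.4% | 80.0% | 86.0% |
| 0.8 | 2.055 | 1.233 | 42.6% | 80.0% | 84.0% |

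Below this range the ordering of the two simpler analyses reverses, but baseline adjustment still does best: at r = 0.3, power is 91.3% for six-month HbA1c alone, 80.0% for change and 93.5% with baseline.

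**Step 4, with condition in the model, as in 8.2.** Variance relative to the baseline-adjusted ANCOVA:

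- six-month HbA1c plus condition: (1 − r²q) / (1 − r²)
- change plus condition: 1 + (1 − r)(1 − q) / (1 + r)

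Example, r = 0.6 and q = 0.3: 0.892 / 0.64 = 1.39 for six-month HbA1c; 1 + 0.4 × 0.7 / 1.6 = 1.18 for change.

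| r | Six-month + condition: variance ratio | Power | Change + condition: variance ratio | Power |
|---|---|---|---|---|
| 0.5 | 1.17–1.27 | 82.0–85.0% | 1.17–1.27 | 82.0–85.0% |
| 0.6 | 1.28–1.45 | 74.0–79.1% | 1.13–1.20 | 81.6–84.0% |
| 0.7 | 1.48–1.77 | 62.8–70.5% | 1.09–1.14 | 81.2–83.0% |
| 0.8 | 1.89–2.42 | 47.6–57.5% | 1.06–1.09 | 80.8–82.0% |

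Ranges run over q from 50% to 20%.

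**The case against.** The strongest reply is that baseline adjustment is already prespecified. SAP 5.3 commits to it in plain terms, as does the protocol twice. The list in 8.2 could be the extra covariates added to a model that already holds baseline. The protocol has that structure: it fixes a baseline-adjusted ANCOVA and then contrasts unadjusted and adjusted analyses, so unadjusted may mean only without the extra covariates. Further, in a 1:1 randomised trial the omission biases nothing and does not inflate type I error for any single prespecified model.

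Much of this stands. A reader might infer that the SAP gave up baseline adjustment; SAP 5.3 says otherwise, so the documents show a contradiction or a drafting slip and no more. A reader might also infer that the trial falls short of its planned power. That follows only if raw six-month HbA1c is modelled without baseline and r is above about 0.5. The SAP names change as the outcome in 2.1, 6.2 and 7, and for change the planned 80% is met. Nor do the documents set out many rival models: with baseline included, 6.2 and the protocol yield the same treatment effect, and it is the list in 8.2 that is out of line.

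What the reply does not remove is that the benign reading has to be supplied by the reader. SAP 5.3 is a data-preparation section; 8.2 specifies the model and omits the term.

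**Conclusion.** The point holds as an internal inconsistency in the specification of the primary analysis. It is not a source of bias, and it is no proof that baseline adjustment was dropped.

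The direction of the precision loss holds for every correlation examined. Its size rests on r and q, which the documents do not give. If change is modelled with condition, the variance is 6% to 27% larger than with baseline adjustment, a modest loss measured against a better analysis and not against the planned power. If six-month HbA1c is modelled with condition, the variance is 17% to 142% larger and power can fall well below 80%.

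The 43% figure is the extreme: six-month HbA1c with no covariates at r = 0.8. It is not the cost of the 8.2 covariate list.

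Two related gaps in the same section remain even when baseline is added: which of the adjusted and unadjusted models is primary, and why the additional covariates differ from the protocol's.

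**What to change.** Revise SAP 8.2 along these lines: *The dependent variable is HbA1c at six months. The primary analysis is an ANCOVA with treatment group and continuous baseline HbA1c as terms, together with [the agreed additional covariates, or none]. The model called unadjusted contains treatment group and continuous baseline HbA1c only. The [adjusted or unadjusted] model is primary.*

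Then:

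- Settle one list of additional covariates. The protocol has age, sex, oral diabetes medicines and insulin; SAP 8.2 has age, sex, household size and condition. Give the reason for any departure from the protocol. Condition is a stratification factor and can stay alongside continuous baseline HbA1c.
- Align SAP 6.2 with the protocol's definition, six-month HbA1c adjusted for baseline. Change can still be described by group, as 8.2 already provides.
- Date the revision and state whether it was made before anyone had seen outcome data by group, since the SAP already reports recruitment as complete.

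The cost is a few sentences. A recent HbA1c is required for eligibility, so the baseline value should exist for every participant. No new data and no change to the sample size are needed.

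### SAP 8.2 does not say which A1c model carries the single p<0.05 test; its covariate list conflicts with the protocol's and omits baseline A1c

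*Combined protocol and SAP*

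**What the plan says.** **SAP 8.2 (Analysis of primary outcome).** A1c is compared between arms by ANCOVA with age, sex, household size and condition (diabetes or prediabetes) as covariates. The section continues: "We will present results of the adjusted and unadjusted models". The decision rule appears once, for the primary analysis in the singular: a p-value below 0.05 "will be sufficient to reject the null hypothesis of no difference". Baseline A1c is not in the covariate list. Oral diabetes treatment and insulin appear only as subgroup interaction variables.

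**SAP 5.3 (Data preparation).** The primary outcome will be adjusted for baseline HbA1c.

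**Protocol, Primary and secondary outcome measures.** The primary outcome is six-month A1c adjusted for baseline.

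**Protocol, analysis paragraphs under Secondary outcome measures.** The primary analysis is an ANCOVA of follow-up A1c adjusted for baseline A1c. The text then promises both an unadjusted analysis of the primary outcome and one "adjusted for age, sex, whether or not prescribed diabetes oral medicines at baseline, and whether or not prescribed insulin at baseline". The same paragraph says that randomization is stratified by site, whereas the protocol's Design section and SAP 2.2 say by condition.

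**Summary of Changes to the Protocol.** No change of covariates is listed.

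**The concern.** A confirmatory test needs one model, fixed in advance. Here the text leaves several candidates: a comparison without baseline A1c, an ANCOVA on baseline A1c alone, the SAP's adjusted model and the protocol's adjusted model. The rule in 8.2 does not choose among them.

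Two things are at stake. If any eligible model may reject the null, the type I error exceeds the nominal 5%. And if one model gives p just below 0.05 and another just above, the documents do not say whether the trial met its primary objective. Prespecification also matters more here because the SAP was written late in an open-label trial: SAP 7 already reports that "A total of 390 participants were recruited".

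**Working it through.** **1. Inputs and the plan's own figure.** SAP 7 gives alpha 0.05, power 80%, a difference of 0.4 percentage points and an SD of 1.3. A two-sided test is assumed for the primary outcome; the protocol states "t-tests to derive two-sided p values" for other continuous outcomes.

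n per arm = 2 × (1.960 + 0.842)² × 1.3² / 0.4² = 2 × 7.849 × 10.5625 = 165.8, so 166 per arm and 332 in total. Dividing by 0.85 gives 390.6, or 391, against 390 stated. The SAP figure reproduces, and it was planned around one two-sided 5% test.

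**2. The covariate lists side by side.**

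| Term | Protocol | SAP |
|---|---|---|
| Baseline A1c | primary ANCOVA | in 5.3, absent from the 8.2 list |
| Age, sex | adjusted model | 8.2 |
| Oral medicines, insulin | adjusted model | subgroups only |
| Household size | no | 8.2 |
| Condition | no (stratifier in Design section) | 8.2 (stratifier in 2.2) |
| Site | no (stratifier in analysis paragraphs) | no |

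The protocol's adjusted list and the 8.2 list share only age and sex.

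**3. Type I error if either of two models may reject.** Under the null, let Z₁ and Z₂ be the treatment test statistics from the smaller and larger model. Their correlation is about ρ = √(1 − R²), where R² is the share of the smaller model's residual variance that the extra terms explain. Then

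error = 1 − P(|Z₁| ≤ 1.96 and |Z₂| ≤ 1.96), for a bivariate normal with correlation ρ.

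The documents give no R², so a range is assumed.

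| Reading of unadjusted | Assumed R² | ρ | Error |
|---|---|---|---|
| Includes baseline A1c | 0.01 | 0.995 | 5.5% |
| | 0.05 | 0.975 | 6.0% |
| | 0.10 | 0.949 | 6.5% |
| Omits baseline A1c | 0.30 | 0.837 | 7.6% |
| | 0.40 | 0.775 | 8.0% |
| | 0.50 | 0.707 | 8.3% |

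For reference, two independent tests would give 1 − 0.95² = 9.75%. No row reaches that.

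**4. Check by simulation** (332 participants, 20,000 null runs in each of three scenarios). Assumed shares of outcome variance were 0.4-0.5 for baseline A1c, 0.02-0.05 for the SAP covariates and 0.02-0.10 for medicines.

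- One prespecified model: 4.9-5.3%.
- Baseline-only or SAP-adjusted: 6.0-6.5%.
- No baseline A1c or SAP-adjusted: 8.0-8.6%. The top value comes from a scenario in which the extra terms explain 0.52 of the variance, just beyond the tabulated range.
- Any of baseline-only, SAP-adjusted and protocol-adjusted: 6.9-8.3%.

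**The case against.** The strongest reply is that no passage declares two primary models. The rule in 8.2 is for one primary analysis, the protocol names baseline-adjusted ANCOVA as that analysis, SAP 5.3 repeats the baseline adjustment, and presenting two models is a reporting statement, not a second test. This stands in part: it would be wrong to say that nothing is named primary anywhere. It does not settle the matter, because two fair readings lead to different models. The protocol sentence points to an ANCOVA on baseline A1c alone; the order of SAP 8.2 points to an ANCOVA with four other covariates.

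A second reply is that the models are highly correlated, so little is gained by choosing between them. This stands as to size. A reader might infer a near doubling of the error rate; the calculation does not support that.

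A third reply concerns the covariates. A reader might infer that the SAP discarded the better predictors by replacing medicines with household size. The documents do not show this. They quantify the prognostic value of neither beyond baseline A1c. Household size sets the voucher amount, and condition is a stated stratification factor, so adding condition is a sound step.

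Finally, the timing might suggest that covariates were chosen after results were seen. Nothing in the documents supports that: complete recruitment is not access to outcomes by arm, and the protocol states that outcome assessors are blinded.

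**Conclusion.** The point holds as an ambiguity in the one confirmatory test. SAP 8.2 does not identify the deciding model, the two documents specify different adjusted models without explanation, and baseline A1c is missing from the list where it matters most. If either model may count, the type I error is about 5.5-6.5% when both include baseline A1c and about 7.6-8.3% when one omits it. Both ranges rest on assumed R² values and on the correlation approximation above. The larger practical risk is a disagreement between models with no rule to resolve it. The issue should be corrected; it does not undermine the design or the sample size.

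**What to change.** Before unblinding, revise SAP 8.2 to:

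- name one primary model: ANCOVA of six-month A1c on treatment, baseline A1c and the stratification factor(s) actually used, plus one fixed list of further covariates;
- reconcile stratification by condition (protocol Design section, SAP 2.2) with stratification by site (protocol analysis paragraphs), so that the model matches how randomization was done;
- align the further covariates between protocol and SAP and record the reason for the change. Whether household size or baseline diabetes medicines are included is the sponsor's choice, provided it is fixed in advance;
- state that the null is rejected only on that model's p-value;
- label every other model a sensitivity analysis, and say for each whether it includes baseline A1c.

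With one model prespecified, the error rate returns to 5%. The cost is wording only: SAP 6.1 already lists age, sex, household size, oral medicines and insulin as baseline data, and baseline A1c and condition are established at enrolment.

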## **Inclusion/Exclusion Criteria**

Participants will be adult (age >19 years) patients of the two participating primary care who have either “pre-diabetes” (A1c 6.0 to 6.4) or diabetes (A1c  $\geq$  6.5) based on bloodwork done in the last 3 months and who either score 2 or above on the six-item food insecurity instrument or who report trouble “making ends meet”. We will exclude people who live with a current study participant (to avoid contamination), people who are palliative (have a life expectancy < 6 months), people with multiple (>3) life-threatening allergies to common foods, people who require total parenteral nutrition, and people with a blood dyscrasia that interferes with hemoglobin A1c testing (anemia due to iron deficiency, B12 deficiency and folate deficiency). We will also exclude individuals with very poorly controlled diabetes (A1c > 11) as interventions other than food such as medicines may be the most important interventions. We will also exclude individuals with very poorly controlled diabetes (A1c > 11) as interventions other than food such as medicines may be the most important interventions.

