###### 2.2 Trial Design

We conducted an open label, parallel two-arm, 1:1 allocation randomized controlled trial. Randomization is stratified by condition: “pre-diabetes” (A1c 6.0 to 6.4) versus diabetes (A1c  $\geq$  6.5).

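### SAP 8.2 tests A1c category conversions by chi-square without baseline A1c, which costs power mainly in the diabetes stratum, and the crossing counts need a label

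*Combined protocol and SAP*

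**What the plan says.** Eligibility in the protocol (Inclusion/Exclusion Criteria) sorts people into pre-diabetes, "A1c 6.0 to 6.4) or diabetes" at 6.5 or above, "based on bloodwork done in the last 3 months". The same two bands define the strata: "Randomization is stratified by condition" (SAP 2.2).

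The protocol (Primary and secondary outcome measures) takes baseline as the most recent value in the three months before enrolment. If several follow-up values exist between 3 and 6 months, "only the later one will be used".

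SAP 8.2 names the test for conversions: "We will also use chi-square tests to compare the proportion of participants". One outcome is a return to normal from the lower entry band ("A1c 6.0 to 6.4) at baseline who convert to a normal hemoglobin A1c"). Its opposite is a rise to 6.5 or more ("and those who convert to diabetes"). SAP 8.2 adds the corresponding downward moves from diabetes. The conversion cut-offs are again 6.0 and 6.5. No confirming value, minimum change or baseline A1c term is given for these tests.

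The continuous A1c outcome is handled differently. SAP 5.3 and the analysis paragraphs closing the protocol's Secondary outcome measures section both adjust it for baseline A1c, although the covariate list in SAP 8.2 does not repeat that term. The same protocol paragraphs give binary outcomes a risk difference with 95% confidence interval as well as a chi-square test.

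**The concern.** Whether someone crosses 6.0 or 6.5 depends heavily on how close to it they started. A participant with diabetes who starts at 6.5 can cross on a 0.1-point fall; one who starts at 9 almost never will. A test that ignores baseline treats this predictable difference as random variation and loses power. The covariate is already collected for everyone.

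The second issue is interpretation. Entry and outcome use the same cut-offs on single values, so a move from 6.0 to 5.9, from 6.4 to 6.5 or from 6.5 to 6.4 is a conversion. That 0.1 is a quarter of the 0.4 points the plan calls clinically important. Some crossings in each arm will reflect measurement variation, and a count of participants who reached normal is easily quoted as clinical change.

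**Working it through.** **The plan's own figure.** The documents state no conversion rate and no A1c measurement SD. The nearest figure to reproduce is the sample size in SAP 7: n per arm = 2(1.960 + 0.842)² × 1.3² / 0.4² = 165.8, so 166 per arm and 332 in total. Then 332 / 0.85 = 390.6, or 391 against 390 stated. It reproduces. This point takes from it only the 0.4 effect.

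**Crossing with no true change.** Assume independent normal error of SD s on each reading, rounding to 0.1, and a flat underlying distribution. Given an observed baseline b, P(follow-up ≤ 5.9) = Φ((5.95 − b) / (s√2)). With s = 0.2, s√2 = 0.283:

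| Baseline | z | P(below 6.0) |
|---|---|---|
| 6.0 | −0.18 | 43.0% |
| 6.1 | −0.53 | 29.8% |
| 6.2 | −0.88 | 18.8% |
| 6.3 | −1.24 | 10.8% |
| 6.4 | −1.59 | 5.6% |

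The mean over the five values is 108.0 / 5 = 21.6%. The same calculation gives 5% at s = 0.05, 11% at 0.1, 29% at 0.3 and 33% at 0.4. The upward crossing to 6.5 is the mirror image.

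The two directions are equal only for a flat or centred distribution. With underlying A1c centred at 6.5 to 7.2 (assumed) and s from 0.1 to 0.3, simulation gives about 9 to 24% downward and 13 to 35% upward.

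**Why baseline matters more in the diabetes stratum.** That stratum runs from 6.5 to 11. With s = 0.2, a baseline of 6.5 gives Φ((6.45 − 6.5) / 0.283) = 43% below 6.5. A baseline of 7.5 gives Φ(−3.71), about 0.01%. The pre-diabetes band is only 0.4 wide, so baseline separates people less there.

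**False-positive rate.** With equal crossing rates of 10 to 30% in both arms and 30 to 80 per arm, the chi-square test rejected in 4.9 to 5.4% of simulated trials. In the power simulations, type I error was about 4 to 6%.

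**Power.** The assumed inputs are:
- 165 participants with diabetes (the documents give no stratum sizes);
- underlying A1c of 5.0 plus a gamma variable (shape 2, scale 0.9), with observed baseline kept if 6.5 to 11.0;
- measurement SD 0.2 and a true effect of 0.4;
- event: follow-up below 6.5, which combines both downward categories.

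The unadjusted test is compared with a likelihood-ratio test for arm in a logistic model containing baseline A1c.

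| SD of true individual change | Unadjusted | Adjusted |
|---|---|---|
| 0.3 | 71% | 90% |
| 0.8 | 40% | 47% |
| 1.2 | 27% | 33% |

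At 600 trials per setting, simulation error near 70% is √(0.7 × 0.3 / 600) = 1.9 points. Repeat runs gave 71 to 76% against 88 to 91% at SD 0.3, 42% against 52% at 0.8, and 27% against 31% at 1.2. The gain is therefore about 15 to 19, 7 to 10 and 4 to 6 points respectively.

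The last row lies closest to the plan's assumed SD of change: √(1.3² − 2 × 0.2²) = 1.27. That figure is trial-wide, not specific to this stratum. In the pre-diabetes stratum the gain was about 1 to 3 points.

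**The case against.** The best defence is that little depends on this analysis. Conversion is not among the seven secondary outcomes in SAP 6.3 and has no hypothesis in SAP 3.2. The primary analysis is continuous A1c by ANCOVA, and SAP 8.2 also describes change by arm and tests an interaction with condition. Randomisation makes measurement variation alike in both arms, and the control arm shows the background crossing rate. The protocol already promises a risk difference with confidence interval for binary outcomes. All of this stands, and it limits the point to precision and labelling. It does not remove the point, because that risk difference would also be unadjusted. It is also fair that the gain shrinks as true individual change grows and is slight in the pre-diabetes stratum.

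A reader might go further and infer that the conversion counts are mostly noise and cannot be used. The documents do not support that. The 10 to 30% range requires that nobody truly changes, and it uses an SD the documents do not give. In a simulation with measurement SD 0.2 and true-change SD 0.3, about 72% of those moving from pre-diabetes to normal had a true fall of at least 0.1. Nor can the plan's SD of 1.3 stand in for measurement error, which would give about 42% each way: it mixes true change with variability in the diabetes stratum.

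A reader might also want conversion redefined to require a 0.4-point change. That makes the effective threshold depend on baseline: someone at 6.0 would have to reach 5.6, someone at 6.4 only 5.9. It also overrides the trial's own category of normal. The plan uses 0.4 as a clinically important difference, not as a rule for classifying individuals.

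**Conclusion.** The point holds as a modest improvement to a supportive analysis. Leaving baseline A1c out of the conversion tests costs power in the diabetes stratum. The loss is large if true individual change is small (about 71% against 90% at SD 0.3) and small if it is near the plan's trial-wide SD (about 27% against 33% at 1.2). These figures rest on an assumed stratum size, measurement SD, effect and A1c distribution.

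The test is not biased and its false-positive rate is not inflated; shared cut-offs might suggest otherwise, but the variation is equal between arms. What cannot be done safely is to read one arm's conversion count as clinical change without the control-arm rate beside it. The primary result is unaffected.

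**What to change.** In SAP 8.2, replace the chi-square tests of conversion with a logistic model in each stratum containing arm and continuous baseline A1c. Report a standardised risk difference with 95% CI: average the predicted probabilities under each arm over all participants in the stratum, then take the difference. Where a category has too few events for a stable model, give the counts and the unadjusted risk difference.

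Keep the plan's definition of conversion. Show the crossing counts for both arms side by side, labelled as supportive and as including measurement variation. A minimum-change definition could be added as a sensitivity analysis, but is optional.

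The cost is a few lines of SAP text and R code, with no new data, visits or tests. SAP 7 reports recruitment as complete, so the change should be dated and made before outcomes are compared by arm. If that comparison has already been made, report the adjusted analysis as post hoc beside the planned chi-square test.
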